### Reimbursement

Participants receive compensation for time and travel in the form of payment for each survey and counseling session completed (i.e., $30 for completing baseline and week 12 surveys, $50 for the 6-month follow-up surveys and $10 for each counseling session). Total compensation is up to $120 for BA and $150 for MI and HE.

### Analyses

#### Power and sample size

Sample size calculations are based on planned comparisons of quit attempts between MI and HE, and MI and BA, and based on conservative (i.e., high) estimates of a 15% and 30% quit attempt rate in the BA and HE arm respectively. The calculations are based on a two-tailed test with an alpha of .05 and a power level of 80%, and an estimated attrition rate of 25%. A sample of 102 per group is necessary to detect a difference of 25% in the proportion of subjects making a 24 hour quit attempt between MI and HE groups, and a sample of 51 per group is necessary to detect a difference of 40% between MI and BA groups. To conserve resources, the study is not powered for all three pairwise comparisons allowing for a smaller BA sample size and the 2:2:1 allocation ratio. For the same reason, the study focuses on building motivation and generating quit attempts and is not powered for the secondary aim of determining group differences in 7-day point prevalence abstinence. The trial aims to obtain effect-size estimates for the MI intervention relative to HE and BA on cessation that will inform future studies. Based on the 2:2:1 allocation ratio the target sample is therefore 255 (102 MI, 102 HE, and 51 BA).

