#### Data analyses

All analyses will be conducted in an intent-to-treat manner. Our primary analyses will utilize a planned comparisons approach to compare the proportion of those making at least one quit attempt for HE and MI, and for BA and MI, using logistic regression. If preliminary analyses comparing groups on baseline variables suggest potential confounding effects by any covariate, these will be included in the logistic regression models. For the secondary hypotheses we will also use logistic regression to compare the effectiveness of HE and MI, and MI and BA, on 7-day point prevalence abstinence at follow-up. To evaluate autonomy support and autonomous regulation as mediators of the presumed effect of MI on quit attempts, and weeks of pharmacotherapy use as a mediator of the presumed effect of MI on cessation, we will follow the procedural steps outlined by Baron and Kenny [38] using logistic regression and the Sobel test [39,40].

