## Discussion

Although MI is a promising tool for healthcare providers who regularly encounter low motivated smokers, stronger evidence for its efficacy is needed to justify the additional training and maintenance of skills needed for this approach. This study is designed to provide the most rigorous evaluation of MI to date, focusing specifically on smokers not motivated to quit and examining quit attempts as the primary outcome. Examination of quit attempts rather than cessation conserves resources but will provide a strong preliminary indication of the potential efficacy of MI for tobacco treatment in this population. A much larger sample size would be necessary to power a trial in which cessation is the primary outcome. However, the secondary outcome of smoking cessation at 6-month follow-up in this study will provide an effect size estimate that can inform the design of future MI trials focused on cessation. On the other hand, should MI fail to prove more efficacious than brief advice or health education, it would encourage reconsideration of the current Clinical Practice Guideline and prompt further research to develop more powerful intervention methods to motivate smokers to try to quit.

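### The promised MI-versus-BA effect size on cessation rests on at most about 8 expected BA abstainers, too few for a standard logistic-regression odds ratio to be relied on

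*Protocol article*

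**What the plan says.** The protocol article's section on power and sample size derives 102 MI, 102 HE and 51 BA participants from quit attempts alone. The inputs are "conservative (i.e., high) estimates of a 15% and 30% quit attempt rate in the BA and HE arm respectively", differences of 25 points (MI–HE) and 40 points (MI–BA), which both imply 55% in MI, and "an estimated attrition rate of 25"%. The section discloses that 7-day abstinence is not powered and that BA was kept small to save resources. It then sets an estimation aim for cessation: "The trial aims to obtain effect-size estimates for the MI intervention relative to HE and BA on cessation that will inform future studies".

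The Discussion repeats this: the cessation outcome "will provide an effect size estimate that can inform the design of future MI trials focused on cessation".

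For the method, the Data analyses section says that "we will also use logistic regression to compare the effectiveness of HE and MI, and MI and BA, on 7-day point prevalence abstinence". It does not say which form of logistic regression is meant or on what scale the effect size will be reported. It also allows baseline variables that look like confounders to enter the logistic models. That sentence follows the primary analysis, and whether it extends to abstinence is not stated.

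**The concern.** Stating that a comparison is unpowered answers a complaint about testing. It does not answer one about estimation, and here the stated purpose is an effect size for designing later trials. Whether the trial can deliver one for MI versus BA depends on how many BA participants are abstinent at 6 months. A smoker who is abstinent for 7 days at follow-up will in practice have made an attempt of at least 24 hours since randomization, so BA abstainers are a subset of BA attempters, and few BA attempters are expected. Logistic regression fitted by maximum likelihood behaves badly with so few events in one arm. The planners of the next trial could receive no finite estimate, or one that a single participant has largely determined.

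**Working it through.** **Plan's own figure.** The protocol gives no expected number or rate of abstainers, so there is no cessation figure to reproduce. The sample sizes concern quit attempts. With two-sided alpha 0.05, 80% power and division by 0.75 for attrition, 30% vs 55% needs 61, then 82 per arm (68 and 91 with continuity correction), against the stated 102. For 15% vs 55% it is 22, then 30 (26 and 35), against 51. Neither figure reproduces, and both are larger than needed. That is a separate matter: the point below uses only the arm sizes and rates.

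**Ceiling from the document.** Expected BA attempters = 51 × 0.15 = 7.65; with 25% attrition, 7.65 × 0.75 = 5.7. Expected BA abstainers reach this only if every attempter is abstinent at 6 months.

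**Below the ceiling.** Let s be the share of attempters abstinent at 6 months. The protocol does not give it, so a range is shown. The BA abstinence probability is p = 0.15s, or 0.15s × 0.75 if the 25% lost are counted as smoking. P(0) = (1 − p)^51, and P(0 or 1) = P(0) + 51p(1 − p)^50.

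| s (assumed) | Expected BA events | P(0) | P(0 or 1) | P(0), lost = smoking |
|---|---|---|---|---|
| 10% | 0.8 | 46% | 82% | 56% |
| 20% | 1.5 | 21% | 55% | 31% |
| 30% | 2.3 | 10% | 33% | 17% |
| 40% | 3.1 | 4% | 18% | 10% |
| 50% | 3.8 | 2% | 10% | 5% |

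**What the odds ratio does.** Take 11 of 102 MI abstainers, close to the expected count at s = 20% (102 × 0.55 × 0.20 = 11.2). For b BA abstainers, OR = (11/91) / (b/(51 − b)), with SE of log OR = √(1/11 + 1/91 + 1/b + 1/(51 − b)). For b = 2: OR = (11/91)/(2/49) = 2.96, SE = 0.789, limits exp(1.086 ± 1.96 × 0.789) = 0.63 to 13.9.

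| BA abstainers | OR | 95% limits |
|---|---|---|
| 0 | no finite value | – |
| 1 | 6.0 | 0.76 to 48 |
| 2 | 3.0 | 0.63 to 13.9 |
| 3 | 1.9 | 0.51 to 7.3 |

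From 1 to 2 events the OR halves; from 2 to 3 it falls by a factor of about 1.5.

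**The alternative on the same data.** The Newcombe interval combines the Wilson limits of the two arms. For 11/102 vs 0/51 the Wilson limits are 0.061 to 0.183 and 0 to 0.070. The difference is 0.108; the lower limit is 0.108 − √((0.108 − 0.061)² + 0.070²) = 0.024, and the upper limit is 0.108 + (0.183 − 0.108) = 0.183. The result is 10.8 points (2.4 to 18.3), where the odds ratio is not finite. For 11/102 vs 2/51 it is 6.9 points (−3.5 to 14.9), which is defined but still wide.

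**Tests.** With MI at 0.55s, BA at 0.15s and no attrition, the Wald test rejects in 10% of trials and the likelihood-ratio test in 47% at s = 20%. At s = 40% the figures are 69% and 81%. The choice of inference within logistic regression matters most when BA events are fewest.

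**The case against.** The strongest reply has four parts.

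- **No cessation rate is given.** A reader might infer that the trial's own rates imply one to three BA abstainers. They do not: the 15% is an attempt rate, and one to three requires s of about 13–39%. Attempters who set a quit date are offered free pharmacotherapy, so s is uncertain. This stands, and only the ceiling comes from the document.
- **A non-finite odds ratio need not be common.** It is common only at low conversion: 46% at s = 10% but 4% at 40% and 2% at 50%. This also stands. The sensitivity to single participants and the wide limits are the sturdier part.
- **The method is not fixed that tightly.** The article says logistic regression. It does not mention maximum likelihood, Wald intervals or an odds ratio as the effect size. Penalised and exact fits are also logistic regression, proportions could be reported too, and an analysis plan not shown may settle this. A reader should therefore not conclude that the plan prescribes an unsuitable estimator. What the article does fix is the promise of an effect size, the BA arm size and the model family, and those sit badly together.
- **No estimator makes up for a small BA arm, and low power is disclosed.** This is true. The Newcombe interval remains wide; at s = 20% it excludes zero in about 34.5% of trials, more than the Wald test but fewer than the likelihood-ratio test. Its merit is that it always exists. The disclosure concerns testing and does not qualify the estimation aim.

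**Conclusion.** The point holds as a limited one. On the plan's own rates, the MI–BA cessation comparison has an expected BA event count no higher than about 7.7 (5.7 after attrition). Under an assumed 10–50% conversion from attempt to abstinence it has about 0.8–3.8. The named model, fitted in the standard way, then returns no finite odds ratio with probability between 46% and 2%. Otherwise it gives one that shifts 1.5- to 2-fold with one further BA participant. The ceiling assumes that abstainers are counted among attempters and that the 15% rate is not exceeded; the rest depends on the assumed conversion.

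The documents do not support reading this as a defect of the trial as a whole, nor as a claim that the cessation analysis will usually fail. Quit attempts, the primary endpoint, are unaffected. It is a cheap improvement to a secondary analysis, together with a correction to what the MI–BA estimate is said to offer.

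**What to change.** 1. Define the effect size for 7-day abstinence as the risk difference with a Newcombe (score) 95% interval, for both MI–HE and MI–BA.
2. If an odds ratio is also given for MI–BA, use Firth-penalised or exact logistic regression, with a profile-likelihood or exact interval respectively, and add no covariates.
3. In the power section and the Discussion, state that the MI–BA cessation estimate rests on few BA events and is imprecise under any method.

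This takes a few sentences and standard software, with no extra participants or data. The costs are slight shrinkage of the penalised odds ratio and a less favourable statement of what the MI–BA estimate can inform.

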#### Data analyses

All analyses will be conducted in an intent-to-treat manner. Our primary analyses will utilize a planned comparisons approach to compare the proportion of those making at least one quit attempt for HE and MI, and for BA and MI, using logistic regression. If preliminary analyses comparing groups on baseline variables suggest potential confounding effects by any covariate, these will be included in the logistic regression models. For the secondary hypotheses we will also use logistic regression to compare the effectiveness of HE and MI, and MI and BA, on 7-day point prevalence abstinence at follow-up. To evaluate autonomy support and autonomous regulation as mediators of the presumed effect of MI on quit attempts, and weeks of pharmacotherapy use as a mediator of the presumed effect of MI on cessation, we will follow the procedural steps outlined by Baron and Kenny [38] using logistic regression and the Sobel test [39,40].

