### Randomization

Prior to starting enrollment a computer-generated randomization sequence was created by the project statistician that determines whether subjects will receive MI, HE, or BA in accordance with the 2:2:1 allocation ratio. The statistician used sequentially numbered opaque envelopes to conceal the group assignment sequence until randomization. Once eligibility is confirmed participants complete the informed consent process. The research assistant then opens the next numbered envelope in the sequence to reveal the participant’s group assignment and the participant begins the computerized baseline survey. In this manner all study personnel remain blind to the condition to which the participant is assigned until after participant’s eligibility is determined and informed consent is obtained.

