### Measures

Participants complete computer-administered assessments at baseline, week 12, and 6-month follow-up. Baseline variables include socio-demographic characteristics (gender, age, education, employment), smoking characteristics (cigarettes smoked per day, number of years smoking, number of prior quit attempts), level of nicotine dependence using the Severity of Dependence Scale [27], and single item measures of motivation and confidence to quit [28-30]. The primary outcome measure is the occurrence of any quit attempt defined as a serious quit attempt of at least 24 hours [31] by 6-month follow-up. The secondary outcome is biochemically verified 7-day point-prevalence abstinence at 6-month follow-up [32,33]. Biochemical verification is conducted by research staff using cotinine test strips for saliva [34]. Hypothesized mediators of MI’s effect on quit attempts are autonomous motivation and autonomy support which are assessed using the Treatment Self-Regulation Questionnaire [35] and the Health Care Climate questionnaire [36,37], respectively. For those who decide to make a quit attempt, weeks of pharmacotherapy use is assessed with a self-report checklist [29] and will be examined as a mediator of MI’s effect on cessation.

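### Covariates enter the primary logistic model only when the randomised groups look different at baseline, so chance imbalance decides the model and the odds ratio it estimates

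*Protocol article*

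**What the plan says.** The Data analyses section describes the primary analysis as follows: "Our primary analyses will utilize a planned comparisons approach to compare the proportion of those making at least one quit attempt". It compares MI with HE and MI with BA by logistic regression. The covariate rule comes next: "If preliminary analyses comparing groups on baseline variables suggest potential confounding effects by any covariate, these will be included in the logistic regression models". No covariate is included unconditionally, and nothing elsewhere in the article makes the unadjusted model primary.

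The Measures section lists the baseline variables, ten in all:
- four socio-demographic: "Baseline variables include socio-demographic characteristics (gender, age, education, employment";
- three on smoking: "smoking characteristics (cigarettes smoked per day, number of years smoking, number of prior quit attempts";
- one on dependence: "level of nicotine dependence using the Severity of Dependence Scale";
- two on readiness: "single item measures of motivation and confidence to quit".

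The Randomization section states that "a computer-generated randomization sequence was created by the project statistician" before enrolment began. Assignments were held in numbered opaque envelopes, opened only after eligibility and consent.

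**The concern.** Confounding at baseline means that assignment depends on a prognostic factor. Concealed randomisation rules this out by design, so a difference seen between arms is a chance event. Comparing the arms therefore answers a question already settled, and it misses the one that matters for precision, namely which variables predict a quit attempt. A prognostic variable that happens to be balanced is left out, and an irrelevant one that happens to differ may be put in.

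Two things are at stake. First, the primary model is not fixed before the data are seen. If the screening is done separately for each comparison, MI against HE and MI against BA could carry different covariates. Second, a logistic odds ratio adjusted for a prognostic covariate is a different quantity from the unadjusted one even under perfect balance, so chance would also decide what the primary estimate means. That matters here because the article intends the trial to supply effect sizes for later trials and to inform the Clinical Practice Guideline.

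**Working it through.** **Inputs from the Power and sample size section.** Control rates: "a 15% and 30% quit attempt rate in the BA and HE arm respectively". The MI rate is 30% + 25 points = 55%, which is also 15% + 40 points. Alpha is 0.05 two-sided, power 80%, attrition 25%, and the arms are 102 / 102 / 51.

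**The plan's own figure.** The article attaches no number to the covariate rule. The nearest stated figure is 102 per group for MI against HE. The stated inputs give 61 per group, or 61/0.75 = 82 after attrition. The gap to 102 is a separate matter. It is relevant here only because it puts the starting power above 80%.

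**Unadjusted power for MI against HE.** With 102 × 0.75 = 76.5, take n = 76 per arm with follow-up. The mean rate is (0.30 + 0.55)/2 = 0.425.

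Power = Φ{[d√n − 1.96√(2 × 0.425 × 0.575)] / √(0.30 × 0.70 + 0.55 × 0.45)}
= Φ{[0.25 × 8.718 − 1.96 × 0.699] / 0.676}
= Φ(1.20) ≈ 88%.

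**How often a screen would flag something (illustration only).** Assume ten independent variables, each tested at p<0.05 in one pairwise comparison. The chance of at least one flag under correct randomisation is 1 − 0.95^10 = 0.40. At p<0.10 it is 1 − 0.90^10 = 0.65. With an assumed common correlation of 0.3 to 0.5 and the 0.05 threshold, it falls to about 35% to 29%. The plan states neither a threshold nor independence.

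**Power under three rules (simulation).** 30% against 55%, 76 per arm, one prognostic score with an assumed odds ratio of 1.65 to 2.7 per SD:

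| Rule | Power |
|---|---|
| Never adjust | about 88–89% |
| Adjust only if imbalanced | about 88–90% |
| Always adjust | about 90–94% |

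The gain from always adjusting is about 1 to 5 points, and the imbalance rule recovers little of it. A second simulation used 77 per arm and ten covariates, three of them prognostic (log odds ratio 0.5 to 0.8 per SD). It gave 87–88%, 88–89% and 93–94%, so the gain depends on how much prognostic information is assumed.

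**Change in the quantity estimated.** The unadjusted log odds ratio implied by the plan is ln[(0.55/0.45)/(0.30/0.70)] = 1.05. In the single-score simulation the mean estimate rose from about 1.06 unadjusted to 1.14–1.29 adjusted, with no confounding present.

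**Type I error.** In the ten-covariate simulation, with equal rates in the two arms, the imbalance rule rejected in 4.3% to 5.2% of trials. No inflation is seen.

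**Events available for a fixed model.**
- All three arms: 0.55 × 102 + 0.30 × 102 + 0.15 × 51 = 94; × 0.75 = 71.
- All three arms if MI does no better than HE: (0.30 × 204 + 0.15 × 51) × 0.75 = 52.
- MI and BA alone: (0.55 × 102 + 0.15 × 51) × 0.75 = 48, of which 0.15 × 51 × 0.75 ≈ 6 are in BA.

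One three-arm model with two arm terms and three covariates has 71/5 ≈ 14 events per term, or 52/5 ≈ 10 in the less favourable case. Five covariates in MI against BA alone would leave 48/6 = 8 per term, with only about 6 events in one arm.

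**The case against.** The best defence is that little harm follows. Type I error holds, and unadjusted power at the design effect is about 88%. Both points stand, and they limit the weight of this point. A reader might infer from the rule that the trial is invalid or underpowered; the article's own rates do not support that.

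A reader might also take motivation, confidence, dependence and prior attempts to be strong predictors that the plan throws away. The article gives no association between any of them and quit attempts. Entry is limited to a motivation score of 6 or less, which narrows the range of that variable. The power gain therefore rests on assumed prognostic strength. The 40% flag rate likewise rests on a screen the plan does not describe and should not be read as this trial's rate.

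The missing threshold and candidate list may sit in a fuller document, and their absence is not counted here. What the article does state is the trigger itself, a comparison of groups. If the reference to confounding also means association with the outcome, the choice becomes more dependent on the data, not less.

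Finally, a fixed unadjusted primary model would remove the discretion equally well and would match the stated aim of comparing proportions. That is fair. Fixed adjustment is preferred because it also uses data already collected. Its small cost is that the primary odds ratio becomes conditional on the covariates.

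**Conclusion.** The point holds in a limited form. The article adopts a rule under which chance imbalance determines the primary model and, through non-collapsibility, the estimand. This is a badly fixed rule and not a detail left to another document. It should be changed, but it does not threaten the validity of the test. The likely loss is about 1 to 5 points of power from a base of about 88%, assuming a prognostic score with an odds ratio of 1.65 to 2.7 per SD, 30% against 55%, and 76 per arm with follow-up. The loss could be smaller if the baseline variables predict weakly. The conclusion that the model is not fixed in advance depends on none of these assumptions.

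**What to change.** Delete the imbalance trigger. Before outcomes are analysed by arm, fix the primary model as arm plus a short set of baseline covariates already collected, for example two or three of dependence, confidence, prior quit attempts and motivation, included whatever the observed balance. Fit all three arms in one model, so that MI against HE and MI against BA use the same covariates and the few events in BA do not have to support a model alone. Report the unadjusted comparison as a sensitivity analysis. Beside the odds ratio, give a standardised risk difference with its 95% CI, which returns the result to the scale of proportions on which the trial was sized and offsets the conditional meaning of the adjusted odds ratio.

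The cost is a change of wording. No new data or participants are needed.

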Equally important for advancing the research on MI is whether the positive effects observed in prior studies can be attributed to the benefits of MI or simply to the greater duration of contact with participants. Teasing out counseling approach effects from general attention effects is critical given the cost and complexity of implementing an MI intervention. For example, studies have shown that significant training and practice is necessary for MI to be properly implemented [16] and there is a lack of research comparing MI with potentially more straightforward but equally intensive interventions (e.g. intensive health education) [12].

A third major concern with the existing evidence base for MI is the lack of attention to the role of motivation. Motivation mediates cessation outcomes and, according to meta-analysis, MI may be more effective for low motivated smokers [17]. Accordingly, there is also evidence that cognitive-behavioral skills training may be more effective than MI for smokers already motivated to make a quit attempt [18]. Taken together, these findings suggest that tailoring counseling style to motivational level may be most effective.

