### Recruitment, participants, and setting

The study is being conducted at a single university-based site in Kansas City, Missouri. The study protocol is in compliance with the Helsinki Declaration and was reviewed and approved by the Institutional Review Board of the University of Missouri – Kansas City (#0978). Smokers are recruited community-wide through word of mouth, newspaper ads, flyers, billboards, internet advertising, and physician referral using printed cards. Recruitment materials invite participation in a study “for smokers” or “smokers not quite ready to quit” and provide a study phone number to call for more information. Potential participants who enquire about the study are informed that the goal is to learn how best to talk to smokers about their health. They are informed that although their smoking will be discussed they will not be required to quit. Eligibility criteria are being 18 years or older, English speaking, reporting smoking a minimum of 1 cigarette per day, having a mailing address and telephone number, willingness to participate in all study components, not currently pregnant or planning to become pregnant in the next 6 months, not currently using a smoking cessation medication, not planning to move from the metropolitan area in the next 6 months, and not currently motivated or ready to quit smoking (defined as scoring 6 or less on a 0–10 point scale of motivation to quit smoking and having no intention to quit in the next 7 days). Potential participants are pre-screened by phone and those likely to be eligible are scheduled for a baseline visit at which time they are re-screened and enrolled if eligible. After the first 24 participants were enrolled, confirmation of self-reported smoking status using a carbon monoxide monitor (Bedfont Scientific piCO + Smokerlyzer®) was added to the re-screen. Eligibility is determined by a CO level of 7 ppm or higher [19,20].

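### The mediation analysis names no covariates, and the plan's only covariate rule is triggered by baseline differences between arms, so a balanced shared cause of mediator and quit attempts can pass for part of MI's mechanism

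*Protocol article*

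**What the plan says.** All quotes are from the protocol article.

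- **Covariate rule (Data analyses).** After the primary comparison the plan says: "If preliminary analyses comparing groups on baseline variables suggest potential confounding effects by any covariate, these will be included in the logistic regression models". The trigger is a comparison of arms at baseline. No other covariate rule appears.
- **Mediation (Data analyses).** The analysis is introduced with "To evaluate autonomy support and autonomous regulation as mediators of the presumed effect of MI on quit attempts", and the method is "we will follow the procedural steps outlined by Baron and Kenny [38] using logistic regression and the Sobel test". No covariate is listed and no sensitivity analysis is mentioned.
- **Mediator instruments (Measures).** Autonomous motivation and autonomy support are "assessed using the Treatment Self-Regulation Questionnaire [35] and the Health Care Climate questionnaire [36,37], respectively".
- **Baseline data (Measures).** The survey includes "single item measures of motivation and confidence to quit", the Severity of Dependence Scale, cigarettes per day and the number of prior quit attempts.
- **Entry limit (Recruitment, participants, and setting).** Low motivation is "defined as scoring 6 or less on a 0–10 point scale of motivation to quit smoking", so baseline motivation can still vary from 0 to 6.

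**The concern.** A Sobel test multiplies two paths: arm to mediator, and mediator to outcome given arm. Randomization protects the first. It does not protect the second, because nobody is randomized to a level of autonomous motivation.

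Participants who start with more motivation or confidence, less dependence or more past attempts may both score higher on the mediator and be more likely to try to quit, in any arm. Such a variable can be perfectly balanced between arms and still confound the second path. A comparison of arms at baseline cannot detect this.

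MI is built to support autonomy, so the first path is expected to be non-zero. A confounded second path then yields a non-zero indirect effect even if the mediator does nothing. What is at stake is the trial's account of how MI works, not whether it works.

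**Working it through.** **1. Two readings of the rule.** The covariate sentence follows the primary comparison, and the mediation sentence comes later.
- If the rule extends to mediation, a balanced variable is left out. With a between-arm test at p<0.05 (an assumed cut-off; the plan gives none), a randomized baseline variable enters in about 5% of trials.
- If the rule is confined to the outcome comparisons, no mediation covariate is named at all.

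Both readings leave a balanced confounder out.

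**2. Inputs.** The plan gives no error rate or power for mediation, so there is no figure of its own to reproduce.
- From Power and sample size: 102 per arm for MI versus HE and 25% attrition, so 102 × 0.75 = 76.5, taken as 76. HE rate 30%; a 25-point difference gives 55% for MI. The log odds ratio is ln(0.55/0.45) − ln(0.30/0.70) = 0.20 + 0.85 = 1.05.
- Assumed, because the documents are silent: the MI effect on the mediator (a = 0.5 or 0.8 SD), the correlation r of the confounder with the mediator, and its odds ratio (OR) per SD for a quit attempt.

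**3. Model, with no mediator effect on the outcome.** X ~ N(0,1); M = aT + rX + e; logit P(Y=1) = logit(0.30) + 1.05T + ln(OR)·X. The Sobel statistic is z = âb̂ / √(â²·se(b̂)² + b̂²·se(â)²). Here â comes from a linear model of M on T, and b̂ from a logistic model of Y on T and M. Each model was fitted without and with X.

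**4. False positives of the Sobel test (1,500 trials per cell), without X / with X.**

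| Per arm | a | r 0.4, OR 1.8 | r 0.5, OR 2.0 |
|---|---|---|---|
| 76 | 0.5 | 9.3% / 1.9% | 20% / 2.0% |
| 76 | 0.8 | 18.1% / 2.8% | 38.1% / 3.4% |
| 102 | 0.5 | 16.9% / 2.1% | 34.3% / 2.5% |
| 102 | 0.8 | 26.1% / 3.9% | 52.3% / 5.3% |

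The false mediator odds ratio is about 1.25–1.40 per SD, and about 11–28% of the total effect is wrongly called mediated. With weak confounding (r 0.3, OR 1.5) the rate is about 3–8% in most settings and up to 11% in the least favourable, against 1–4% with X included.

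**5. Does the imbalance rule help?** A second simulation (1,000 trials per cell; r 0.4, log OR 0.7, i.e. OR e^0.7 = 2.01) let X enter only if the arms differed at p<0.05.

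| Per arm | a | X never | X by the rule | X always | X entered |
|---|---|---|---|---|---|
| 76 | 0.5 | 12.7% | 12.3% | 1.3% | 4.9% |
| 76 | 0.8 | 25.3% | 23.5% | 2.5% | 5.2% |
| 102 | 0.5 | 22.9% | 22.4% | 2.4% | 5.1% |
| 102 | 0.8 | 36.8% | 35.2% | 3.2% | 4.5% |

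The rule removes at most two percentage points. With no confounding at all, the unadjusted test rejected in 1.1–3.9% of trials, so the excess comes from the omitted variable.

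**6. Two refinements.**
- If a significant total effect is also required, as the Baron and Kenny steps ordinarily do, the highest rate at 76 per arm falls from 38% to 30%.
- If the confounder is measured with an assumed reliability of 0.6, adjustment still leaves 3–14%.

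**The case against.** The strongest objection is that the article is silent, not wrong. A reader might infer that the plan tests the mediators with no adjustment. It does not say so, and a journal article commonly leaves a covariate list for a secondary analysis to the full protocol or analysis plan. This disposes of any claim that the plan rules adjustment out. It does not dispose of the point: the article does state a covariate rule, and its trigger is the wrong kind for mediation models if it is carried over to them.

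Four further objections have weight.

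- **Two mediators, one argument.** Baseline motivation is close in content to autonomous motivation. Autonomy support is the participant's view of the counselor, and a strong correlation with baseline motivation is less obvious. With an assumed r of 0.1–0.2 and OR of 1.5–1.8, false positives are 1.6–6.2% at 76 per arm and 2.2–8.8% at 102.
- **Assumed strengths.** No document gives r, the odds ratio or MI's effect on the mediator. The entry limit of 6 or less may weaken the confounding.
- **The Background sentence.** It reads "Motivation mediates cessation outcomes and, according to meta-analysis, MI may be more effective for low motivated smokers". A reader might take this as the authors' own statement that baseline motivation predicts quit attempts. It says that motivation mediates cessation, which is a different claim, so the confounding rests on plausibility.
- **The remedy is imperfect.** Motivation and confidence are single items, so adjusting for them reduces the bias without removing it.

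Mediation is also neither the primary nor the secondary outcome.

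**Conclusion.** The point holds in a limited form. On either reading of Data analyses, a baseline variable that is balanced between arms but drives both mediator and quit attempts stays out of the mediation models. Part of an MI effect could then be wrongly attributed to the mediator, chiefly autonomous motivation and less clearly perceived autonomy support.

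The size rests on assumed strengths. With no true mediator effect and 76–102 per arm, Sobel false positives are about 3–8% under weak confounding (up to 11% at worst) and about 8–50% under moderate to strong confounding (r 0.4–0.5, OR 1.8–2.0). They are somewhat lower if a significant total effect is also required. With adjustment for a well-measured confounder they are about 1–4%, with one cell at 5.3%.

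A shared cause alone is not enough: MI must also shift the mediator and, under Baron and Kenny, affect quit attempts. The trial hypothesizes both. The randomized comparisons of quit attempts and the sample size are not affected.

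**What to change.** In Data analyses, state three things.

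1. Both the mediator model and the outcome model of the mediation analysis include a short prespecified set of baseline variables already collected (motivation, confidence, Severity of Dependence score, prior quit attempts), regardless of balance between arms. Use a smaller set for MI versus BA. There, expected events among completers are 0.55 × 76 + 0.15 × 38 = 41.8 + 5.7, about 48, where 38 is 51 × 0.75 rounded down. Arm, mediator and four covariates would already be six coefficients.
2. A sensitivity analysis shows how strong an unmeasured or poorly measured mediator-outcome confounder would have to be to remove the indirect effect.
3. The mediation results are described as exploratory.

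The cost is a few sentences and a few degrees of freedom, with no new data. The primary analysis need not change.
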